### Control group

CG participants will follow the usual flow of the waiting list of patients awaiting outpatient physical therapy in the public healthcare system and will not receive any guidance or exercise, as recommended in pragmatic studies. They will be monitored weekly by telephone call to check the onset of outpatient physical therapy and adverse events. Like the TG, the period each CG participant will spend in the trial will depend on the time awaiting outpatient physical therapy. Participants in both the TG and CG will not be prohibited from receiving others interventions such as exercises on their own, physical activity (e.g., walking), medications, or physical therapy elsewhere while on the waiting list, but this information will be recorded.

### Data collection

Figure 2 shows the schedule of enrollment, interventions, and assessments (according to the SPIRIT). Outcomes will be assessed by in-person meetings at baseline (t0), at the end of the telerehabillitation protocol (t1), and after discharge from outpatient physical therapy or within 6 months of outpatient treatment (t2). All evaluations will be performed by a trained evaluator blinded to group allocation. All instruments show adequate validity and reliability for older adults [48–52].

**Fig. 2 Fig2:**
[figure not shown]
Schedule of enrolment, interventions, and assessments (according to SPIRIT)

In the baseline (t0), besides the outcomes, socio-demographic and clinical data will be collected, as well as data on the companion, and information on the use of communication technologies.

In the second evaluation (t1), satisfaction with the intervention and the TG app will also be evaluated. To minimize sample loss, the second evaluation will occur before the start of outpatient physical therapy or up to 1 week after the start of physical therapy treatment. The start of the outpatient physical therapy will be accompanied by weekly phone calls to both groups.

The final evaluation (t2) will take place on the last day of outpatient physical therapy or up to 1 week after discharge. The evaluation will consist of the collection of outcomes and information about outpatient physical therapy. Reasons for program discontinuity and follow-up losses will be recorded throughout the study.

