**Methods:**

This is a pragmatic randomized controlled clinical trial with two groups: telerehabilitation and control. Participants (n=230) will be recruited among individuals discharged from hospitals who are in the public healthcare system physical therapy waiting lists. The telerehabilitation group will receive a smartphone app with a personalized program (based on individual’s functional ability) of resistance, balance, and daily activity training exercises. The intervention will be implemented at the individuals’ homes. This group will be monitored weekly by phone and monthly through a face-to-face meeting until they start physical therapy. The control group will adhere to the public healthcare system’s usual flow and will be monitored weekly by telephone until they start physical therapy. The primary outcome will be a physical function (Timed Up and Go and 30-s Chair Stand Test). The measurements will take place in baseline, start, and discharge of outpatient physical therapy. The economic evaluations will be performed from the perspective of society and the Brazilian public healthcare system.

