### Outcomes

#### Primary outcome

The primary outcome will be physical function measured by the Timed Up and Go (TUG) and the 30-s Chair Stand Test (30CST). These tests were chosen because they are simple, fast, widely used and do not require special equipment.

The TUG was developed to measure the functional mobility of older people [53]. The participant gets up from a chair and walks 3 m alone or with the aid of a walking device, at a comfortable and safe speed, and then return and sit down again in the same chair [53].

The 30CST consists of sitting and standing, tasks often performed daily [54, 55]. This test was developed as a measure of lower limb strength for older adults [49]. The participant sits in a chair with arms crossed in front of the torso and must repeatedly stand and sit for 30 s as fast as possible [56].

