### Strengths and weakness

This pragmatic study will be developed in the context of the public healthcare system, which favors—if our hypothesis is proven right—a simple and direct application in clinical practice. To reduce the risk of bias, the protocol will be prospectively recorded, the sample size will be representative of the population of interest, participants will be randomly allocated to groups, the allocation process will be concealed, the evaluators will be blinded to the group allocation, and data will be analyzed by intention-to-treat. Blinding participants and physical therapists to the intervention will not be possible due to the nature of the intervention.

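### Items on satisfaction with the intervention and the app sit inside the t1 evaluation, which the protocol assigns to a blinded evaluator, so an evaluator who collects them learns the arm

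*Protocol article*

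**What the plan says.** Under Data collection, the article describes three in-person assessments: "Outcomes will be assessed by in-person meetings at baseline (t0), at the end of the telerehabillitation protocol (t1"), and a third (t2) linked to discharge from outpatient physical therapy. It then states: "All evaluations will be performed by a trained evaluator blinded to group allocation".

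The text below Figure 2 adds to the middle visit: "In the second evaluation (t1), satisfaction with the intervention and the TG app will also be evaluated". For t2 it says: "The evaluation will consist of the collection of outcomes and information about outpatient physical therapy".

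The arms differ in what there is to rate. From the Abstract (Methods): "The telerehabilitation group will receive a smartphone app with a personalized program". From Control group, on the controls: "will not receive any guidance or exercise, as recommended in pragmatic studies".

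Strengths and weakness lists among the measures that reduce bias that "the evaluators will be blinded to the group allocation". It concedes that blinding is impossible only for participants and physical therapists.

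**The concern.** The satisfaction items are specific to one arm. A control participant has no app and no programme, so the questions cannot be put to both groups in the same form. Anyone who asks them, or sees that they do not apply, knows the allocation.

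The primary outcome is at stake: "The primary outcome will be physical function measured by the Timed Up and Go (TUG) and the 30-s Chair Stand Test (30CST"). Both tests are run by the evaluator and depend on participant effort. The TUG is timed at a pace the participant chooses, and the 30CST counts stands done as quickly as possible. Instruction, encouragement, stopwatch handling and the decision to count an incomplete stand can all shift with knowledge of the arm. Participants and therapists are already unblinded, so the evaluator is the remaining blinded party in the measurement of these outcomes. t1 is also the end of the intervention period.

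**Working it through.** The protocol states no figure on this point that could be reproduced, so the check sets its statements side by side.

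1. **Who assesses.** Data collection gives all evaluations to a blinded evaluator, immediately after naming t0, t1 and t2 as in-person meetings.
2. **What t1 contains.** The text below Figure 2 calls t1 the second evaluation and adds the satisfaction items to it. It names no separate interviewer, no self-completed form and no order relative to the functional tests.
3. **Who can answer.** Only the TG has the app (Abstract, Methods). Controls get no guidance or exercise (Control group). Asking the items identifies TG, and not asking them identifies control.
4. **Could the sentence mean something else?** The Canadian Occupational Performance Measure, under Secondary outcomes, also yields a satisfaction score. That score rates performance of a self-care activity, applies to both arms, and is already an outcome. The t1 sentence concerns the intervention and the app, and describes something collected in addition.
5. **Which measurements are exposed if the evaluator collects the items.**

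| Visit | Items before the tests at t1 | Items after the tests at t1 |
|---|---|---|
| t0 | Not affected: allocation follows the initial evaluation | Not affected |
| t1 TUG and 30CST | Unblinded | Still blinded as far as these items go |
| t2 TUG and 30CST | Unblinded if the same person assesses | Unblinded if the same person assesses |

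6. **How many participants.** Sample size gives 115 per group, 230 in total. Up to 115 would be asked directly, and up to 230 could be classified by whether the items are used. With the planned 15% abandonment, 115 × 0.85 = 97.75, about 98 per group, would remain.
7. **Size of bias.** The document contains nothing on how much an unblinded evaluator shifts TUG or 30CST, so no bias can be computed.

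In either order, an evaluator who collects the items is no longer blinded when t1 ends. The two statements conflict unless someone or something other than the evaluator collects the items, and the article does not provide for that.

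**The case against.** The t1 sentence is passive: it says the items will be evaluated, not by whom or how. Self-completion, or collection by other staff, would leave outcome measurement blinded. The trial already has channels that bypass the evaluator: the app, where participants rate pain and difficulty after each exercise, and a weekly online form used for the costs. Satisfaction with the intervention is not listed as an outcome, so the blinding sentence could be read as covering outcome measurements only. Figure 2 is not visible in the text reviewed, and a fuller protocol may settle who hands over the questionnaire.

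This stands as a limit on certainty: the article does not show that the evaluator will ask the questions. It does not remove the conflict, because the article uses the same word for the t1 visit and for what the blinded evaluator performs. If the items are handled elsewhere, the blanket statement still needs the exception written in.

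A second objection is that the TUG is a stopwatch time and the 30CST a count, both less open to interpretation than a rated scale, and that unblinded participants may reveal their arm anyway. Both are fair. But chance disclosure is partial, whereas a scheduled questionnaire could reveal the arm of every participant assessed.

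Two stronger readings are tempting and not supported:

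- A reader might infer that blinding is certainly broken at both t1 and t2. That needs the items to precede the tests, or one person to assess both visits. The article states no order, and refers to one evaluator under Data collection but to several under Strengths and weakness.
- A reader might assume a shift in the evaluator's measurements and derive an inflated type I error. Such a figure would rest on an invented shift, on that shift reaching the whole TG at the analysed time point, and on a simple two-group test in place of the planned mixed model.

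**Conclusion.** The point holds as an unresolved conflict between two statements. Followed literally, the protocol has a blinded evaluator conduct a t1 evaluation that includes items only one arm can answer. That undercuts a safeguard the protocol claims for its primary outcome.

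The consequence is conditional. If the evaluator collects the items before the tests, t1 is unblinded. If after, t2 is unblinded only when the same person returns. Up to 115 TG participants are directly exposed, and up to 230 indirectly. The direction and size of any bias cannot be determined from the document. Because an evaluator cannot be re-blinded, this should be settled before the first t1 assessment.

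**What to change.** Remove the satisfaction and app items from the evaluator's t1 assessment. Collect them on a self-completed form, in the app or through the existing online form, after the t1 functional tests, and withhold the answers from the evaluator. If the online platform is used, keep these items apart from the weekly cost reports, since Economic evaluation reserves those data for blinded researchers. Tell participants not to mention the app or their group to the evaluator. State the arrangement under Data collection, so that the claim that all evaluations are blinded is true as written.

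The monitoring therapists should not ask the items instead. People tend to rate a programme kindly when the person who delivered it asks. The last weekly call also may not be known in advance, because the intervention stops when the participant is called for outpatient therapy.

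The cost is one questionnaire moved to an existing channel, with no extra visit or staff. The downside is possibly slightly lower completion of the satisfaction items, which are not among the primary or secondary outcomes.

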### Outcomes

#### Primary outcome

The primary outcome will be physical function measured by the Timed Up and Go (TUG) and the 30-s Chair Stand Test (30CST). These tests were chosen because they are simple, fast, widely used and do not require special equipment.

The TUG was developed to measure the functional mobility of older people [53]. The participant gets up from a chair and walks 3 m alone or with the aid of a walking device, at a comfortable and safe speed, and then return and sit down again in the same chair [53].

The 30CST consists of sitting and standing, tasks often performed daily [54, 55]. This test was developed as a measure of lower limb strength for older adults [49]. The participant sits in a chair with arms crossed in front of the torso and must repeatedly stand and sit for 30 s as fast as possible [56].

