### Sample size

The sample size was based on the TUG primary outcome. An effect size of d=0.4, previously obtained by Brovold et al. (2012) [65], power of 80%, alpha of 0.05, and abandonment rate of 15% were considered to estimate sample size using the G*Power 3.1 software. This resulted in a minimum sample size of 230 participants, 115 per group.

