### Data analysis plan

The outcome variables and the participants’ characteristics will be analyzed with descriptive statistics. The Kolmogorov-Smirnov test will be used to test the normality of the data. Comparison of TG and CG baselines will be conducted with parametric or non-parametric test.

Outcome group comparisons will be analyzed with the nonlinear mixed effect model [66], given that deconditioning follows a nonlinear path over time and the period individuals remain in the study is not homogeneous. Since the intervention time will be different among the participants, time will be treated as a random factor.

All data will be analyzed for intention-to-treat; that is, all random participants will be included in the analysis regardless of adherence to the protocol. The data will be analyzed by the R software (R Foundation for Statistical Computing, Vienna, Austria) with a significance level of 5%.

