## Discussion

### Potential impact and significance

Our hypothesis is that the multi-component program offered by telerehabilitation will minimize the deconditioning of hospital discharged older adult patients waiting for physical therapy and will reduce costs. Older adults who were hospitalized due to different health conditions and who experienced functional decline have up to five times greater likelihood of dying and 10 to 20 times greater chance of being readmitted after hospital discharge [67–69]. In addition, studies show that approximately 30% of these older individuals have functional losses at the moment of hospital discharge [68, 69] and that roughly the same proportion maintain these losses 30 days after discharge [69]. The type of intervention most recommended for this population is a multicomponent program [2, 45]. Thus, the faster these older individuals start physical therapy and remove themselves from inactivity, the less negative will be the impacts and deconditioning advancement. The costs for patients and the public healthcare system may be reduced. Telerehabilitation reduces the cost of transportation [23–25]. Once deconditioning is associated with readmissions [1–3] and hospitalization generates cost to the healthcare system, the exercise program may reduce hospital readmissions.

In Brazil, telerehabilitation is still not a common practice, with a higher concentration of investments aimed towards telehealth. In low- and middle-income countries, studies using the remote rehabilitation are incipient. Due to the COVID-19 pandemic, this rehabilitation modality has been gaining prominence as an alternative to face-to-face treatment [70]. The pandemic has impacted health services around the world, particularly non-urgent treatments. There is no estimate regarding the end of social isolation measures in many countries, and it is not possible to predict when healthcare services will return to normality. Waiting lists for outpatient services will possibly be even longer after the pandemic. As such, telerehabilitation is becoming increasingly essential to ensure treatment for the general population.

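### Two measures are primary, with no rule for success and no primary visit, while the sample size covers one TUG comparison

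*Protocol article*

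**What the plan says.** - **Measures.** Protocol article, Primary outcome: "The primary outcome will be physical function measured by the Timed Up and Go (TUG) and the 30-s Chair Stand Test (30CST". The abstract says the same. Neither place ranks the two tests, combines them into one score, or says whether one or both must show a benefit.
- **Visits.** Data collection places outcome assessment at baseline, "at the end of the telerehabillitation protocol (t1), and after discharge from outpatient physical therapy or within 6 months of outpatient treatment (t2"). The abstract gives the same schedule: "The measurements will take place in baseline, start, and discharge of outpatient physical therapy". No follow-up visit is called primary.
- **Sample size.** "The sample size was based on the TUG primary outcome". The inputs are "An effect size of d=0.4" with "power of 80%, alpha of 0.05, and abandonment rate of 15% were considered to estimate sample size using the G*Power 3.1 software", and the result is 230 participants, 115 per group.
- **Analysis.** The Data analysis plan compares the groups with a nonlinear mixed effect model, "with a significance level of 5" per cent. It names no contrast or visit as the deciding one.
- **Hypothesis.** Under Potential impact and significance, the programme "will minimize the deconditioning of hospital discharged older adult patients waiting for physical therapy".

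**The concern.** The Primary outcome section has two primary measures, but the Sample size section is written as if there were one. With two measures, two follow-up visits and no rule for success, several readings of a positive trial fit the text, and each has different error and power. If either test may win, the chance of a false claim exceeds the stated 5%. If both must win, the stated 80% power is not delivered. If the choice is still open when the data are in, it can follow the results.

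The choice of visit also changes the question. The hypothesis is about people waiting for therapy. The intervention stops when therapy is about to begin, so t1 measures its effect over the wait. t2 comes after a course of outpatient therapy in both arms and answers a different question.

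**Working it through.** **1. The plan's own figure.** Inputs from the Sample size section: d=0.4, power 80%, alpha 0.05, abandonment 15%. Allocation is 1:1 (Randomization and allocation). Sidedness is not stated; two-sided is assumed.

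- Two-sample t-test with the noncentral t distribution: 99.08 per arm, rounded up to 100.
- 100 × 1.15 = 115 per arm, so 230 in total. This matches exactly.
- A one-sided test gives 180 to 184 in total and does not match.
- Dividing by 0.85 instead gives 200 / 0.85 = 235.3, so 236. The difference of 6 does not matter here.

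The 230 therefore pays for one measure and one comparison. Expected completers are 115 × 0.85 = 97.75, about 98 per arm.

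**2. Either measure may win, one visit, each tested at 5%.** Family-wise error = 1 − P(|Z1| < 1.96 and |Z2| < 1.96), with Z1 and Z2 bivariate normal with correlation ρ. For ρ = 0 this is 1 − 0.95² = 0.0975.

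**3. Both measures must win, one visit, each at 5%.** The type I error is at most 5%. Assume d=0.4 on both. The noncentrality is 0.4 × √(98/2) = 2.8, and power per test is about 0.80 (normal approximation). For ρ = 0 the joint power is 0.7996² = 0.639.

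| Assumed correlation | Error if either may win | Power if both must win |
|---|---|---|
| 0 | 9.8% | 64% |
| 0.5 | 9.1% | 69% |
| 0.7 | 8.3% | 71% |
| 0.8 | 7.8% | 73% |
| 0.9 | 7.0% | 75% |

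**4. Each visit also tested separately (conditional).** Four tests at 5% give 1 − 0.95⁴ = 18.5% if independent. Simulation with 1,000,000 draws, under two correlation patterns, gives about 16% at correlation 0.5, 13 to 14% at 0.7, and 9 to 10% at 0.9. This applies only if the visits are tested separately and any win counts.

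**5. What keeps both properties.**

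- One primary comparison: 5% error and about 80% power at 230.
- Bonferroni over two measures (0.025 each): 121 evaluable per arm, so 121 × 1.15 = 139.15, or 140 per arm and 280 enrolled. Dividing by 0.85 gives 143 per arm and 286. At 230 enrolled, power per test is 70.6%.

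**The case against.** The strongest reply is that the article already points to an answer. It sizes the trial on TUG, and its aim and hypothesis concern the waiting period, so TUG at t1 is the natural reading. It adds that a multiplicity procedure can properly sit in an analysis plan that is not shown here. Both points are fair, and the absence of an alpha-splitting scheme is not held against this article. But a natural reading is not a designation. The article itself makes two measures primary, and the measure and visit that define success belong in the protocol.

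A reader might infer more than the text supports:

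- **That four comparisons are all primary, each at 5%, with error near 19%.** The article calls no visit primary and states 5% once. The mixed model may give one overall group or group-by-time test per measure, so there may be two tests, not four. Independence is also implausible for two function tests repeated in the same people.
- **That the trial has no control of type I error.** A both-must-win rule would control it. What is missing is the statement of which rule applies.
- **That the arms will be alike at t2.** Nothing in the article says so. It supports only that t2 follows outpatient therapy in both arms, and t2 may fall within 6 months of that treatment instead of at discharge.

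It also stands that the both-must-win power is illustrative, because no effect on 30CST is given.

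**Conclusion.** The concern holds in this form: the primary endpoint is not fixed to one measure, one visit or one rule for success, and the sample size matches only one of the possible readings. Under an either-wins rule at one visit, the error is about 7 to 10%. Under a both-must-win rule, power is about 64 to 75%. These figures rest on assumed correlations from 0 to 0.9, two-sided tests, about 98 completers per arm and, for power, d=0.4 on both measures. The higher range of roughly 9 to 19% would apply only if each visit is also tested separately, which the plan does not fix.

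The figure of 230 is not itself wrong. It is right for one TUG comparison, so the repair needs no more participants. The matter should be settled before outcomes are compared by arm, because it governs the trial's main claim.

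**What to change.** State in the Primary outcome, Sample size and Data analysis plan sections that:

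1. the single primary endpoint is the between-group difference in TUG at t1, tested at two-sided 5%;
2. 30CST at t1 is tested next at 5%, and only if TUG is significant;
3. all t2 comparisons are secondary, because both arms have had outpatient therapy by then.

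This fixed sequence holds the family-wise error for the two t1 tests at 5%, keeps the planned power for TUG and leaves the sample size at 230. It costs one paragraph in the protocol, with matching entries in the analysis plan and the registry, and adds no visits. The downside is that a benefit on 30CST cannot be claimed on its own if TUG is not significant. If the sponsor wants both measures to carry equal weight, an alpha split or a both-must-win rule is also valid. The sample size must then be recalculated; the Bonferroni version needs 280 to 286 enrolled.
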